### Fidelity of Treatment Receipt

We will also assess participant factors related to treatment fidelity, i.e., how the treatment is received by the participant. This involves an assessment of individual factors such as comprehension of information, and the ability to use and perform skills associated with both the data collection and behavioral elements of the study. We have a standardized interactive learning module to teach the participant how to input symptoms on the wrist-worn accelerometer. Because the validity of the symptom information is central to our tailoring methods, all participants will undergo this learning module prior to their first session with the OT. In addition, both the tailored and general activity pacing interventions include strategies to ensure comprehension of the material. For example, participants are asked to reiterate main pacing concepts back to the therapist (e.g., importance of planning, resting before symptoms get worse, etc.). Participants also receive homework assignments that reinforce the lessons presented during the session and are asked to complete a daily activity logbook. Both of these homework items are used to assess personal compliance and overall protocol adherence. Each subsequent session involves a review of previously presented topics, a review of goals, and time for discussion of any barriers. Session 3 is focused on relapse-prevention, and continues the theme of setting goals and problem-solving to minimize barriers that impede the use of activity pacing. Lastly, we conduct debriefing interviews with each participant to examine their experiences in the intervention including adherence with activity pacing in daily life at the end of their involvement in the study.

### Measures

The primary outcome measures are fatigue and pain. Fatigue is assessed in two ways. First, fatigue is measured by the Brief Fatigue Inventory (BFI) [51], a reliable and valid measure of fatigue in adults with cancer. There is no gold standard measure of fatigue for adults with OA; however, the BFI is of particular relevance because it assesses fatigue by asking about interference in daily life, which is our primary interest. This scale is usually scored by calculating an overall score based on an average of 9 of the 10 items. In samples with rheumatic conditions, the BFI has recently been divided into two fatigue subscales (fatigue severity and fatigue interference) [52]. Although no studies have examined the clinical significance of these subscales in OA or in other samples, we are expecting similar or greater improvements in fatigue severity and fatigue interference as seen in our pilot study (8% and 15% improvement respectively) [41]. Second, because there is currently no commonly-used fatigue measure in OA across studies, an additional method of assessing fatigue from the Patient-Reported Outcomes Measurement (PROMIS) assessment tools will be used. PROMIS is a collection of carefully constructed item banks that can be used to assess multiple domains of relevance to complex and chronic illnesses. Due to the methods used to construct these item banks, such measures are expected to be more precise and less burdensome to patients to complete [53]. We are using the 8-item short form PROMIS fatigue scale [54]. Pain, the other primary outcome, is assessed by the Western Ontario and McMaster Universities Osteoarthritis Index (WOMAC). This is a validated, disease-specific questionnaire for adults with knee or hip OA in which participants rate their currently experienced pain and physical disability [55]. Based on previous studies, we will consider a 2 point decrease on the WOMAC pain scale to be clinically significant [56].

Other secondary outcomes and potential moderators include physical function, assessed by the 6 Minute Walk Test [57], a commonly used, validated measure of physical performance in adults; arthritis self-efficacy, the perceived ability to manage arthritis and pain and fatigue symptoms, measured by the Arthritis Self Efficacy Scale [58]; and other variables such as knee extension strength (as measured by a hand-held dynamometer), and general health status variables (e.g., BMI, self-reported chronic conditions, depression using the Geriatric Depression Scale [59], medication use). In addition, PA will be assessed by a wrist-worn accelerometer [Actiwatch-Score, Phillips Respironics-Mini Mitter Co, Bend OR] that measures changes in acceleration. Although it is worn on the wrist, it is highly associated with whole-body movement [60,61]. Changes in acceleration are recorded as activity counts and saved every 15 seconds. Higher activity counts reflect participation in higher intensity activities [62,63]. PA from the accelerometer will be aggregated in different ways. We will look at average activity counts and total activity counts that occur: 1) in the time between symptom reporting periods, 2) over each day, and 3) over the entire home monitoring period similar to our previous studies [40,41,64].

### Procedure for the Home Monitoring Periods

The accelerometer is mounted on each participant's non-dominant wrist. Participants are instructed on how to enter responses into the accelerometer using a standardized interactive learning module that we have developed and used in previous studies. Participants are given the opportunity to practice rating their symptoms and using the accelerometer's input button to record the information. If, for some reason, participants fail the learning module (e.g., inability to rate symptom experience on a numeric rating scale, inability to press the input button) they are excluded. Although we have not encountered exclusion for this reason in any of our past studies, this reporting is central to the tailoring portion of the intervention and therefore is an important criterion for study inclusion. Participants also become familiar with the logbook that accompanies the accelerometer and serves to cross-validate the items. The logbook is used as a back-up if there are missing data from the accelerometer.

Momentary pain and fatigue severity are measured on 0 -10 numerical rating scales that will be directly input into the accelerometer five times a day (at rise time in the morning, 3 times during waking hours, and at bedtime). The accelerometer is worn for 7 days at baseline and at the outcome assessment periods. Pain is rated on a scale from 0 = no pain to 10 = pain as bad as you can imagine. Fatigue, defined as tiredness or weariness [28], is rated on a scale from 0 = no fatigue to 10 = fatigue as bad as you can imagine. Momentary ratings are used in the study for the sole purpose of generating tailored reports on individual symptom-activity relationships during the baseline week for the tailored activity pacing intervention.

### Data Analysis

The target sample size in this study is 156 participants. In our recruitment plans, we have factored in a 30% attrition rate to achieve this number. Although there are three arms to the study: tailored activity pacing, general activity pacing, and usual care group, the study was powered to find effects between the two active intervention groups (tailored activity pacing and general activity pacing). Specifically, the power analysis was based on our pilot data in which we compared the tailored activity pacing intervention with the general activity pacing intervention and detected large group differences using the effect size Cohen's d [65] on BFI fatigue severity and interference (d = .79 and 1.1 respectively) at 10 week-follow-up. Based on a 2 group t-test at a significance level of p = .05, we will have greater than 90% power to detect an effect size of .74 or larger with 40 people in each of the two active intervention groups. Because most people with OA do not receive this type of intervention, it is important to compare the active intervention groups to a group receiving usual care. The study was powered to detect treatment effects between the active intervention groups; therefore we will also have sufficient power to detect differences between the active intervention groups and usual care group.

To examine the effectiveness of a tailored activity pacing intervention on fatigue, pain, and physical function, we will use repeated measures analysis of variance (RM ANOVA) models to analyze the responses (pain, fatigue, and 6 minute walk test) at baseline, 10 weeks, and 6 months for the three treatment groups (tailored activity pacing, general activity pacing, and usual care group). This will allow us to estimate the effects of treatment group, time point and the treatment × time interaction. Similarly, we will use RM ANOVA models to determine if increased arthritis self-efficacy post intervention is related to improvements in symptom severity and function and to evaluate the effect of tailored activity pacing on physical activity.

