## Methods/Design

This is a three-arm randomized controlled trial that will examine outcomes at baseline, posttest (approximately 10 weeks post baseline), and 6 months. Ethical approval for this study was obtained by the University of Michigan Medical School Institutional Review Board and the Subcommittee on Human Studies in the Veteran's Affairs Ann Arbor Healthcare System. The overall goal of the study is to examine the effectiveness of a tailored activity pacing intervention for adults with symptomatic knee or hip OA. The primary outcomes are fatigue and pain.

The specific aims are:

Aim 1: To examine the effectiveness of a tailored activity pacing intervention on fatigue, pain, and physical function.

Aim 2: To determine if increased arthritis self-efficacy post intervention is related to improvements in symptom severity and function.

Aim 3: To evaluate the effect of tailored activity pacing on physical activity.

Eligible individuals are randomly stratified by age and gender into one of three arms: tailored activity pacing intervention, general activity pacing intervention, or usual care. The tailored and general activity pacing interventions are equivalent in session number and length. Participants are involved in study procedures over 6 months. For the intervention groups, involvement consists of 3 individual sessions, 3 testing visits, 3 home monitoring periods, 3 weekly follow-up phone calls, and monthly contact phone calls until the outcome assessment at 6 months. The usual care group participates in all activities described above except for the intervention sessions and the 3 weekly follow-up phone calls.

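### On the most natural reading, 156 participants with 30% attrition leave about 36 per arm, not the 40 behind the stated power of more than 90% (about 87% instead); a minor correction

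*Protocol article*

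**What the plan says.** Everything needed stands in one paragraph of the protocol article, under Data Analysis, apart from the number of arms.

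- The total: "The target sample size in this study is 156 participants".
- The allowance, in the next sentence: "In our recruitment plans, we have factored in a 30% attrition rate to achieve this number".
- The test: "Based on a 2 group t-test at a significance level of p = .05".
- The power claim: "we will have greater than 90% power to detect an effect size of .74 or larger", and this is tied to a number per arm, "with 40 people in each of the two active intervention groups".
- The number of arms, under Methods/Design: "Eligible individuals are randomly stratified by age and gender into one of three arms".

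The paragraph adds that the study is powered for tailored against general activity pacing. The effect size rests on pilot differences of d = .79 (fatigue severity) and 1.1 (fatigue interference) at the 10-week follow-up. It then carries the power statement over to the comparisons with usual care.

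The article does not give the inflation formula, the allocation ratio or the size of the usual care group. It does not say outright whether 156 counts people before or after attrition.

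**The concern.** A target, an attrition rate, a number per arm and a power are all printed, so they should agree. On the most natural reading they do not. Three arms of 40 make 120, and 156 is exactly 30% more than 120. But adding 30% of the required number does not protect against losing 30% of those enrolled, because the loss is taken from the larger number. To keep a required number after a loss rate of 30%, one divides by 0.7.

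At stake is the accuracy of the headline power figure. As the working shows, 40 per arm is the smallest whole number that gives 90% power at d = .74, so the claim has almost no slack and any shortfall in completers takes it below the stated level. The same statement is extended to usual care, so a shortfall there would count as well.

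**Working it through.** **Inputs from the article:** total 156; attrition 30%; 40 per active arm; d = .74; significance level .05; two-group t-test; three arms.

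**Assumptions, because the article is silent:** equal allocation; 40 also required for usual care; a two-sided test. Power is from the noncentral t distribution.

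**1. Reproduce the stated power.** With n = 40 per arm and d = .74, power is 90.5%. The number needed for 90% is 39.4 per arm, so 40 after rounding up. The claim of more than 90% at 40 per arm is correct as it stands.

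**2. Reproduce the stated total.**
- Required completers: 3 × 40 = 120.
- By multiplication: 120 × 1.30 = 156, which matches exactly.
- By division: 120 / 0.70 = 171.4, so 172 (or 3 × 58 = 174 with three equal whole arms). Neither gives 156.

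**3. What 156 enrolled would leave.**
- 156 × 0.70 = 109.2 in total, and 109.2 / 3 = 36.4 per arm.
- Shortfall: 120 − 109.2 = 10.8, about 11 completers.
- Largest attrition that still leaves 120: 1 − 120/156 = 23.1%.

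**4. Power and detectable effect by number per arm (two-sided .05).**

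| Completers per arm | Power at d = .74 | Power at d = .79 | d detectable with 90% power |
|---|---|---|---|
| 36 | 87.2% | 91.1% | .775 |
| 36.4 | 87.6% | 91.4% | .770 |
| 40 | 90.5% | 93.7% | .734 |
| 52 | 96.2% | 97.9% | .642 |

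At 36 per arm, power for the larger pilot effect (d = 1.1) is 99.6%.

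**5. The other reading of 156.** If 156 is the number remaining, there are 156 / 3 = 52 per arm, the last row of the table, and the power claim is met with room to spare. Recruitment would then have to be 156 / 0.70 = 222.9, about 223, a figure the article does not print.

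**The case against.** The strongest objection is textual. Taken literally, the sentence on attrition says that recruitment was planned so as to reach 156, which makes 156 the number left. Power is then 96%, and 40 per arm can be read as a number that suffices rather than the number planned. This stands as a possible reading, so a reader who infers that no reading reconciles the figures goes too far. Its weakness is that it explains neither why power is stated at 40 rather than 52 nor where 156 comes from, and it makes the exact match with 120 × 1.3 a coincidence.

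Other points on that side:

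- **The mechanism is inferred.** One might state as fact that the authors multiplied. The article prints no formula; the exact match makes multiplication likely, no more.
- **An unequal split.** 40 / 0.7 rounds up to 58, and 58 + 58 + 40 = 156, which would keep 40 in each active arm (58 × 0.7 = 40.6). Nothing in the article supports unequal allocation, and this split gives usual care no allowance although the 30% is stated without restriction.
- **A one-sided test.** At 36 per arm it would give 92.8% power. None is stated, and the two-sided test reproduces the claim at 40.
- **Timing.** The pilot effects are at 10 weeks, while follow-up runs to 6 months, and the article does not say when the 30% accrues. If it is the 6-month figure, loss at 10 weeks could be 23% or less. The Procedures section also describes consent and the monitoring week before randomisation, so some loss may come earlier. These points stand: the shortfall depends on the full 30% being lost, after allocation, by the time point analysed.
- **Size.** Even at 36 per arm, the effect detectable with 90% power is below both pilot effects. This stands and sets the severity.

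**Conclusion.** The stated figures need reconciling, and the matter is minor. If 156 is the enrolled number, allocation is equal, the test is two-sided and 30% are lost by the analysed time point, about 36 per arm remain. Power at d = .74 is then about 87% rather than more than 90%: a loss of about 3 percentage points and 11 completers. If 156 is the number after attrition, there is no power shortfall, but the paragraph then bases its power on a number per arm that is not the planned one and omits the recruitment total.

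A reader might infer that the trial is underpowered or must enrol more. The documents do not support that: at the smaller pilot effect, d = .79, 36 per arm still give about 91% power. Nothing in the design or analysis has to change.

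**What to change.** State whether 156 counts participants before or after attrition, and give the resulting number per arm.

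- **If before:** either restate the power as about 87% for d = .74 (equivalently 90% for d = .77) with 30% attrition, or say that more than 90% power at d = .74 holds only if attrition is at most 23%.
- **If after:** state the recruitment total (about 223) and give the power at 52 per arm (about 96% for d = .74) in place of the figure at 40.

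It would help to add, in the same sentence, the allocation ratio and the time point to which the 30% applies, because the result depends on both.

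The cost is a sentence or two of wording and, on the first reading, a slightly less favourable power figure. No extra enrolment is needed.

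### RM ANOVA in its classical form would drop observed 10-week data from anyone missing the 6-month visit, although 30% attrition is expected; a likelihood-based mixed model would keep them

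*Protocol article*

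**What the plan says.** The Data Analysis section of the protocol article names one method for the outcomes of the effectiveness aim: "we will use repeated measures analysis of variance (RM ANOVA) models to analyze the responses (pain, fatigue, and 6 minute walk test", measured "at baseline, 10 weeks, and 6 months for the three treatment groups". Baseline is thus one of the responses. On the output of the model it adds: "This will allow us to estimate the effects of treatment group, time point and the treatment × time interaction". RM ANOVA is named again for the self-efficacy aim and the physical activity aim.

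On numbers, the same section says "The target sample size in this study is 156 participants" and then "In our recruitment plans, we have factored in a 30% attrition rate to achieve this number". It gives neither the timing of the loss nor its split by arm. The power statement is "Based on a 2 group t-test at a significance level of p = .05", with "greater than 90% power to detect an effect size of .74 or larger with 40 people in each of the two active" intervention groups. The pilot effects behind it were seen "at 10 week-follow-up".

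The section does not mention a mixed model, a likelihood fit or a rule for missed visits. It also does not say that people with a missed visit are excluded. Elsewhere, the home monitoring section offers the logbook as a back-up for accelerometer data. That provision does not extend to the fatigue, pain or walk-test outcomes.

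**The concern.** RM ANOVA as ordinarily understood works on a complete set of repeated responses per person. With three time points, someone who attends at 10 weeks but not at 6 months leaves the analysis altogether, and the 10-week measurement goes too. The Procedures section describes contact during weeks 11 to 23 intended to secure the 6-month assessment, so loss after week 10 is a pattern the investigators themselves foresee.

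Two things are at stake. One is precision at the time point on which the power analysis rests. The other is validity: people who complete all visits may differ from those who do not, and if they differ in a way that depends on the arm, the treatment contrast at 10 weeks shifts. The point concerns a method the article names. It is not a complaint that detail is missing from a condensed report.

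**Working it through.** **Inputs from the Data Analysis section:** d = .74; 40 per active arm; two-group t-test at .05; target 156; attrition 30%; pilot effects at 10 weeks.

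**Assumptions, because the article is silent:** two-sided test; equal allocation, 156 / 3 = 52 per arm; loss equal in the arms unless stated otherwise.

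**1. The stated power.** For n per arm, the noncentrality is d × √(n/2) with 2n − 2 degrees of freedom. With n = 40: .74 × √20 = 3.31, critical value 1.99, power 90.5%. This reproduces the stated figure of more than 90%.

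**2. Completers against all observed 10-week data, if 156 are enrolled.** Completers are 52 × .70 = 36.4 per arm. If a share f of the 30% loss comes before week 10, the number with 10-week data is 52 × (1 − .30f).

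| Share of loss before week 10 | With 10-week data, per arm | Power | Completers, per arm | Power | 10-week values dropped, three arms |
|---|---|---|---|---|---|
| none | 52 | 96.2% | 36.4 | 87.6% | 46.8 |
| half | 44.2 | 93.1% | 36.4 | 87.6% | 23.4 |
| all | 36.4 | 87.6% | 36.4 | 87.6% | 0 |

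These use the article's own t-test at 10 weeks, so they show the order of the loss and not the exact power of either repeated-measures model.

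**3. If 156 is the number remaining.** Then 52 per arm complete and completers-only power is 96.2%. The article's wording allows either reading. The arithmetic 40 × 3 × 1.3 = 156 points towards enrolled, but does not settle it.

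**4. Bias in the contrast at 10 weeks.** Simulation with 1,000,000 per arm, SD 1, equal correlation r between visits, and 30% lost. Loss before week 10 is completely at random. Loss after week 10 depends on the 10-week score through a logistic slope of 1 per SD. The contrast is the difference between arms in change from baseline to 10 weeks, among completers; the truth is −.74. The main runs put half the loss after week 10:

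| Dropout after week 10 | r = .5 | r = .6 |
|---|---|---|
| completely at random | −.74 | −.74 |
| same dependence and same rate in both arms | −.74 | −.74 |
| dependence in one arm only | −.82 or −.66 | −.80 or −.68 |
| opposite dependence in the two arms | −.90 or −.59 | −.86 or −.62 |

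The two figures in a cell belong to the two possible directions. The shift is therefore about .06 to .08 SD for one arm and .12 to .15 SD for opposite dependence, or roughly .07 and .14. With a true difference of zero the shifts were the same size. They grow if all the loss comes after week 10; the largest, with opposite dependence and r = .4, was about .30. Equal dependence but 40% against 20% loss, all after week 10 and with r = .5, gave −.82 or −.66 according to which arm lost more.

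The contrast from all observed 10-week values stayed at −.74 throughout. The completers' contrast at 6 months also stayed at about −.74, which follows from the equal correlations assumed and should not be generalised.

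**The case against.** The strongest reply is that the article nowhere restricts the analysis to people with all three visits. Group, time and interaction effects can equally come from a likelihood-fitted repeated-measures model that keeps partial records, and such detail may stand in a full protocol or analysis plan that is not shown. This stands as far as it goes: a reader might infer that the article prescribes a completers-only analysis, and it does not say so. But the method it names, in its ordinary meaning, is the complete-data procedure, and nothing in the section points to another. If a mixed model was meant, the wording should say so.

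A second reply is that the tailored and general arms, the powered comparison, are matched in number and length of sessions and in later contact, so dropout that differs between them is not much to be expected. This also stands. Differential dropout is more plausible against usual care, which receives neither sessions nor weekly follow-up calls.

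A third reply is that opposite dependence in the two arms is close to a worst case, and that even the sign of the bias is an assumption. Agreed: the runs show what can happen, not what will.

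Finally, a mixed model is no cure-all. It is unbiased when data are missing at random given what is observed, not when dropout depends on unseen values, and it cannot recover 10-week data lost before week 10.

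**Conclusion.** The concern holds in conditional form. The article commits to RM ANOVA on three visits with 30% attrition expected. Fitted classically, that analysis discards observed 10-week values, between none and about 47 over the three arms if 156 are enrolled. In the middle case it means 87.6% power in place of 93.1% at d = .74. These figures rest on equal allocation, on 156 being the number enrolled, and on an assumed timing of the loss.

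A reader might go further and conclude that the trial falls short of its stated power. The documents do not support that: if 156 remain after attrition, completers alone give about 96%. Nor do they support a claim that the comparison of tailored with general pacing will be biased. Bias needs a dropout rate or mechanism that differs by arm; in that event shifts of about .07 to .14 SD in either direction are plausible illustrations when half the loss comes after week 10.

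This should be fixed: a better analysis of the same data is available at almost no cost. It does not show the trial to be unsound.

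**What to change.** In the Data Analysis section, replace RM ANOVA with a linear mixed model for repeated measures, fitted by restricted maximum likelihood with an unstructured covariance and a group-by-time term. Include all randomised participants in their assigned arm, with every observed visit. State that the model is valid under missing at random, and add a sensitivity analysis for departures from that assumption. Keep the completers' RM ANOVA at most as a secondary check. State also whether 156 is the number enrolled or the number expected to remain, since the size of the loss depends on it.

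The cost is a change of analysis wording and a little more analysis work. No further data, visits or participants are needed, and standard software suffices.

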**Discussion:**

Managing OA symptoms during daily life activity performance can be challenging to people with knee and hip OA, yet few clinical interventions address this issue. The activity pacing intervention tested in this trial is designed to help people modulate their activity levels and reduce symptom flares caused by too much or too little activity. As a result of this trial, we will be able to determine if activity pacing is more effective than usual care, and among the intervention groups, if an individually tailored approach improves fatigue and pain more than a general activity pacing approach.

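### The effects named for the repeated measures ANOVA are not the tailored-versus-general contrast the trial is powered on; a baseline-adjusted contrast would supply it at no cost

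*Protocol article*

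**What the plan says.** All places are in the protocol article.

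- **Question.** The Discussion part of the abstract says the trial will show, among the intervention groups, "if an individually tailored approach improves fatigue and pain more than a general activity pacing approach". Comparison with usual care is also an aim.
- **Power.** Data Analysis says "the study was powered to find effects between the two active intervention groups". The basis is pilot effects on "BFI fatigue severity and interference (d = .79 and 1.1 respectively) at 10 week-follow-up". The calculation takes a two-sample t-test at the 5% level with 40 participants per active arm and concludes: "we will have greater than 90% power to detect an effect size of .74 or larger".
- **Analysis.** The next paragraph of Data Analysis fits a repeated measures ANOVA to fatigue, pain and the 6-minute walk at baseline, 10 weeks and 6 months in all three arms. Of this model it says: "This will allow us to estimate the effects of treatment group, time point and the treatment × time interaction".
- **Randomisation.** Methods/Design says: "Eligible individuals are randomly stratified by age and gender into one of three arms".

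The article names no tailored-versus-general contrast within the ANOVA and no visit at which it would be read. It does not use baseline as a covariate.

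**The concern.** The power statement and the analysis statement describe different tests. The first is a two-arm comparison. The second lists a group effect and an interaction, each spread over three arms and three visits, one of which precedes randomisation.

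Two consequences follow if the listed effects are taken as the results.

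- The group effect averages in a visit at which no treatment difference can exist, so it understates the effect and loses power.
- The interaction can be significant only because usual care differs from the two pacing arms. It would then say that pacing helps and nothing about tailoring.

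A significant ANOVA could therefore be reported without answering the question on which the sample size rests. The choice of contrast and visit would also remain open after the data are seen.

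**Working it through.** **Inputs from Data Analysis.** Effect 0.74 SD, 40 per active arm, significance level 0.05 (taken as two-sided, which reproduces the stated power), three arms, three visits including baseline.

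**Assumptions, not in the article.** SD 1 at every visit, the same correlation r between any two visits with r = 0.3, 0.5 or 0.7, no expected baseline difference, 40 in each of the three arms, and an effect of 0.74 at both follow-ups unless stated.

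**1. The plan's own figure.** For the two-group t-test the noncentrality is 0.74/√(2/40) = 3.309 on 78 df, which gives power 0.905. The normal approximation gives 0.911. The stated power above 90% reproduces.

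**2. Tailored versus general under three estimators.** The noncentrality is effect/√(2v/n), where v is the per-person variance of the summary used. The error df are 117, from three arms of 40, and 116 with a baseline covariate.

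| Estimator | Effect | v | v at r = 0.3 / 0.5 / 0.7 | Noncentrality | Power |
|---|---|---|---|---|---|
| Group effect, mean of three visits | 0.74 × 2/3 = 0.493 | (1+2r)/3 | 0.533 / 0.667 / 0.800 | 3.02 / 2.70 / 2.47 | 0.85 / 0.76 / 0.69 |
| Change from baseline to 10 weeks | 0.74 | 2(1−r) | 1.40 / 1.00 / 0.60 | 2.80 / 3.31 / 4.27 | 0.79 / 0.91 / 0.99 |
| 10 weeks adjusted for baseline | 0.74 | 1−r² | 0.91 / 0.75 / 0.51 | 3.47 / 3.82 / 4.63 | 0.93 / 0.97 / 0.996 |

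With the two-arm 78 df the last group-effect figure is 0.68 instead of 0.69. If the difference exists at 10 weeks only, the group effect estimates 0.74/3 = 0.247 and has power 0.32 / 0.27 / 0.23.

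**3. Gain from adjustment.** The variance of the adjusted contrast relative to the change contrast is (1−r²)/[2(1−r)] = (1+r)/2, or 0.65 / 0.75 / 0.85. Put the other way, the change contrast carries 54% / 33% / 18% more variance.

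**4. Omnibus interaction.** Suppose tailored and general are identical and both beat usual care by 0.74 at both follow-ups. The squared interaction effects sum to 0.74² × (2/3) × (2/3) = 0.2434. The noncentrality is 40 × 0.2434/(1−r) = 13.9 / 19.5 / 32.5 on 4 and 234 df, and the rejection probability is 0.86 / 0.96 / 0.998. If only tailoring works (0.74, 0, 0), the sum is the same 0.2434 and so are the probabilities. The test cannot tell the two situations apart.

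**5. Sensitivity to the number per arm.** The article gives 156 participants and 30% attrition but no allocation ratio. With equal arms, 156/3 = 52. If 156 are enrolled, 52 × 0.70 ≈ 36 per arm remain. If 156 are completers, 52 remain. Powers are for r = 0.3 / 0.5 / 0.7.

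| Per arm | t-test | Group effect | Change to 10 weeks | Baseline-adjusted |
|---|---|---|---|---|
| 36 | 0.872 | 0.810 / 0.719 / 0.640 | 0.748 / 0.875 / 0.980 | 0.903 / 0.949 / 0.992 |
| 40 | 0.905 | 0.850 / 0.764 / 0.687 | 0.792 / 0.907 / 0.989 | 0.931 / 0.966 / 0.996 |
| 52 | 0.962 | 0.928 / 0.865 / 0.798 | 0.887 / 0.963 / 0.998 | 0.976 / 0.991 / 0.999 |

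**The case against.** The strongest reply is that the sentence lists what the model estimates and does not say which test decides the trial. The fitted model contains the tailored-minus-general difference at every visit, the abstract says that comparison will be made, and an article may leave the contrast statement to a fuller plan. This stands. A reader might infer that the trial cannot test its own question, and the article does not support that.

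Four further points also stand.

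- Rejecting the omnibus null when usual care differs is a correct rejection, and comparison with usual care is a stated aim. The harm arises only if that result is read as evidence for tailoring.
- It would be wrong to say that baseline information is wasted. The interaction uses it through change. At 40 per arm the 10-week change contrast matches the planned t-test at r = 0.5 and beats it above that. For a sustained effect, mean follow-up minus baseline has power 0.89 / 0.97 / 0.998 from the same model. Like for like, adjustment is still better: 0.992 / 0.996 / above 0.999.
- A reader might call the absence of age and gender from the model an error. A condensed article need not list covariates, and their absence does not alter which contrast is tested.
- The abstract names both 10 weeks and 6 months for outcome assessment. The article ties 10 weeks to the pilot effects behind the power calculation and does not declare it the primary visit.

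What the reply leaves untouched is that the model, responses, visits and effects are all stated, none of the stated effects is the powered contrast, and a more efficient form of that contrast is available.

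**Conclusion.** The point holds as a recommended improvement. The powered comparison and the named effects do not match. The group effect recovers two thirds of a sustained difference, and at the article's own 40 per arm its power is below the stated 90% throughout the range examined. The omnibus interaction is uninformative about tailoring in particular. The change contrast falls below 90% at 40 per arm only when r is below about 0.5. The baseline-adjusted contrast stays above 90% across the range, even at 36 per arm.

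The dilution to two thirds needs only an equal effect at both follow-ups, and the ratio (1+r)/2 needs only equal variances at the two visits compared. The power figures rest on the assumed r, the compound symmetry and the number per arm, so they should be read as ranges.

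**What to change.** Replace the description of the analysis with the following.

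- Take the 10-week and 6-month values as responses, with arm, visit, arm by visit and the baseline value of the outcome as covariate. A longitudinal model that keeps baseline as a response but constrains the arms to a common baseline mean is equivalent for this purpose.
- Preferably add the stratification factors, age and gender.
- Report tailored minus general at 10 weeks, the time point of the pilot effects used for power, with its 95% CI, as the main comparison.
- Report the 6-month contrast and the contrasts with usual care separately.
- Keep the omnibus tests as descriptive and state that they are not evidence for tailoring.
- Show power as a range over r and over the number per arm after attrition.

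The cost is analysis wording only. Every variable is already collected, and no participant, visit or measurement is added.
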